**Fig. 1 Fig1:**
[figure not shown]
DVD Delivery Pathway

The actors in the DVD are real patients who have undergone surgery for removal of cancers from various head and neck sites, and health professionals (doctors, nurses, allied health) who patients will encounter during their journey.

#### Usual care

Usual care patients will have access to the standard resources and services currently available to patients undergoing surgery for head and neck cancer. This includes the [25].

### Data collection

Data will be collected using a self-administered survey (one for patients and one for partners, carers or family members) at three time points i.e.,; baseline (prior to surgery), post-surgery (usually at follow up clinic) and 3 months post-baseline. Information about how the resource is being used and who is using it will also be collected via phone call at T2.

Those participants randomised to the intervention group will receive the intervention DVD to take home and a follow-up phone call will be made with a week to ensure they are clear about how to use the DVD. Follow up surveys will be conducted at the post-op clinic visit and again at 3 months post-surgery. At time point 2 participants will again be contacted by phone to discuss how the resource is being used and to identify any concerns that may have arisen. A standardised discussion guide with questions regarding the DVD will be used and handwritten notes taken. The 3 month follow up may be conducted via post, telephone or web survey (Fig. 2).

**Fig. 2 Fig2:**
[figure not shown]
Study timeline

### The survey tool

The survey tool comprises a number of validated tools that have been used widely in patients who have had treatment for cancer. Demographic data such as age, postcode, marital status, income and level of education along with general health information will also be collected. Prior to commencement of the study the survey was piloted with 11 patients 6 family members and modified according to feedback. The original survey was reduced in size as patients reported it was too time consuming to complete, particularly in the clinic context.

Table 1 summarises all variables that will be measured and psychometric properties of the measures that will be used, the primary and secondary outcomes and moderators that will be surveyed, including the chosen measures. Outcome selection was based on Lazarus and Folkman’s (1984) Stress and Coping framework [26], where outcomes either characterise the coping process (appraisal, dyadic and individual coping strategies, and self-efficacy) or indicate the extent to which the coping process was successful in addressing stressors (mental health and well-being outcomes: anxiety, cancer distress, depression, quality of life, and relationship satisfaction). Anxiety and empowerment are the primary outcomes, as the DVD intervention focuses on coping strategies to manage high levels of anxiety directly and/or cope with cancer demands known to trigger anxiety. The degree to which participants feel challenged and supported at each time point will also be measured using a five point Likert scale.

**Table 1 Tab1:** Outcome measures

Outcomes	Measures and psychometrics	
	Patients	Partners
Anxiety	7-item HADS-Anxiety subscale [28] (α = .68−.93)	
Depression	7-item HADS Depression subscale [28] (α = .68−.93)	
Appraisal	28−item Kessler Cognitive Appraisal of Health Scale [29] (α > .70)	28-item Kessler Cognitive Appraisal of Health Scale [29] [adapted] (α > .70)
Self-efficacy and empowerment	12-item Communication and Attitudinal Self-Efficacy Scale for cancer [30] (CASE-Cancer; α = .76−.77) 29-item Strategies Used by People to Promote Health (SUPPH, α = .76−.92 [31] 10-item Perceived Efficacy in Patient-Physician Interactions (PEPPI, α = .91) [32]	12-item Communication and Attitudinal Self-Efficacy Scale for cancer [30] (CASE-Cancer[adapted]; α = .76−.77) 29-item Strategies Used by People to Promote Health (SUPPH, α = .76−.92) 48-item Caregiver Empowerment Scale (α = .76−.92) 10-item Perceived Efficacy in Patient-Physician Interactions (PEPPI, α = .91)
Shame and Stigma Scale in head and neck cancer	20-item Shame and Stigma Scale in head and neck cancer [33]	
Information needs	37-item Cancer Information Needs Survey [34]	

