**Design/Methods:**

A randomised clinical trial pre and post intervention design, comparing the use of a tailored DVD intervention, provided preoperatively and used throughout the post- operative period, with usual treatment. One hundred fifty-six individuals or partner couples will be randomly recruited into either the intervention or control group. A survey will be administered at three time points, preoperatively, post operatively and 3 months post-surgery. Anxiety and empowerment are the primary outcome measures. Qualitative data about use of the resource will be gathered by phone interview.

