## Methods/Design

### Study design

A multicentre randomised pre and post intervention design controlled trial (RCT) testing the effectiveness of a DVD information resource intervention. The overall aim of this study is to evaluate impact on mood, coping and self- efficacy, together with the utility of the first DVD education intervention designed to meet the information needs of head and neck cancer patients who undergo surgery in Australia and their partners and family members.

The primary hypothesis is: Patients and carers in the intervention group will report lower anxiety post-op and 3 months post-baseline compared to those in the control group.

The secondary hypothesis is: Patients and carers in the intervention group will report lower depression and symptom distress, fewer unmet information needs, and feel better prepared for the various steps in their treatment compared to those in the control group.

The study was funded by a Hunter New England Health District Innovation Support Grant.

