### Participants

Participant inclusion criteria are:Group 1. Adults aged 18 and over who have been diagnosed with a primary, early-stage head and neck cancer, whose treatment plan includes surgery.Group 2. Partners or family members aged 18 and over involved in the care and support of patient participants from Group 1.

Participants will need sufficient fluency in English and be able to participate in the study. While the aim is to recruit dyads where possible, consenting patients whose partner, carer or family member does not consent to participate, will still be eligible.

In accordance with our sample size calculation 156 (78 in in the intervention group and 78 in the control group) will be recruited into the study. If they have a partner, carer or family member who is also willing to participate they will be recruited and provide ‘linked’ data to the patient’s responses. Therefore we aim to recruit 156 individual patients or patient couples (total 156 to ≤312 individuals). The probability is 80 % that the study will detect a minimum important difference of 1.5 on HADS scores at a one-sided 0.05 significance level.. This is based on the assumption that the standard deviation of the response variable is 3.75

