### Data analysis

Intention-to-treat and per protocol analysis will be conducted. The primary outcome, anxiety will be measured repeatedly across the three time periods and, therefore, analysed using generalised linear mixed models (GLMM). In this context, the GLMMs are similar to linear regression models, but take account of the correlation between repeated measurements on individuals. Their advantage over a traditional repeated measures analysis of variance is that they use all available data under the assumption that missing data are missing at random. Sensitivity analysis will explore the robustness of this assumption. GLMM will also be used to explore the secondary outcome measures. The study is powered on a sample of individual patients. Partners were outside the calculation and are a secondary outcome only.

Qualitative data collected at phone interview (or face to face if possible) at time point 2 will be transcribed, coded and themed to produce a descriptive account of participants’ views about the resource and experiences of using the DVD resource.

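### The protocol names its primary outcome in two incompatible ways (anxiety with empowerment, or anxiety alone), while its sample size supports only one HADS comparison

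*Protocol article*

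**What the plan says.** The protocol article identifies the primary outcome in four places, and they disagree.

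- Abstract, Design/Methods: "Anxiety and empowerment are the primary outcome measures".
- The survey tool: "Anxiety and empowerment are the primary outcomes, as the DVD intervention focuses on coping strategies".
- Study design, primary hypothesis: "Patients and carers in the intervention group will report lower anxiety post-op and 3 months post-baseline compared to those in the control group". Only anxiety is named, at two follow-up times, in patients and carers.
- Data analysis: "The primary outcome, anxiety will be measured repeatedly across the three time periods and, therefore, analysed using generalised linear mixed models (GLMM"). The outcome is singular, and empowerment is not mentioned.

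The secondary hypothesis reads "Patients and carers in the intervention group will report lower depression and symptom distress, fewer unmet information needs, and feel better prepared" and goes on to treatment preparedness, so empowerment is not there either. In Table 1 it shares a row with self-efficacy. That row lists for patients "12-item Communication and Attitudinal Self-Efficacy Scale for cancer [30] (CASE-Cancer; α = .76−.77) 29-item Strategies Used by People to Promote Health" and then PEPPI, which makes three scales; partners have the same three plus a caregiver scale. No scale is marked as the primary one.

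The Participants section sets 78 patients per arm, with 80% power to "detect a minimum important difference of 1.5 on HADS scores at a one-sided 0.05 significance level" and a standard deviation of 3.75. It names neither the HADS subscale nor the time point. Data analysis adds that partners lie outside this calculation and are secondary.

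**The concern.** Which outcome is primary is decided in this article, and it is decided twice with different answers. A later analysis plan can add detail but cannot make both statements true. A report could present a result on anxiety or on empowerment as primary and cite the article in support either way. Participants are unblinded and the outcomes are self-reported, so pre-specification is one of the main safeguards against selective reporting.

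The conflict also reaches the statistics. Empowerment, if primary, has no hypothesis, no chosen scale and no power basis. Even on the anxiety-only reading, the hypothesis covers two follow-up times, and the article does not say whether one must succeed, both must, or a single model contrast decides. It includes carers, whom the analysis section makes secondary. The late time point also varies: 3 months after baseline in the primary hypothesis, 3 months after surgery in the abstract, and both in Data collection.

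**Working it through.** **Inputs from the document (Participants):** difference 1.5, SD 3.75, one-sided alpha 0.05, power 80%, 1:1 allocation, 78 per arm. The correlations used below are not in the document. They are assumptions and are shown as ranges.

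**1. The stated sample size.**
n per arm = 2 × (1.645 + 0.842)² × 3.75² / 1.5² = 77.3, rounded up to 78, or 156 in total. This matches exactly. The noncentral t calculation also gives 78 (power 80.0%). A two-sided 0.05 test would need 99 per arm. The figure is therefore one one-sided comparison with the whole alpha spent on it.

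**2. False-positive rate if any one success is enough, each test at one-sided 0.05.**
Independent tests: 1 − 0.95^m. Correlated tests: 1 − P(all Z < 1.645) under a multivariate normal with equal correlation r.

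| Reading (patients) | m | r = 0 | r = 0.3 | r = 0.5 | r = 0.7 |
|---|---|---|---|---|---|
| Anxiety at two times, or anxiety and one empowerment scale at one time | 2 | 9.75% | 9.3% | 8.8% | 8.0% |
| Anxiety and three empowerment scales, one time | 4 | 18.5% | 16.4% | 14.4% | 12.0% |
| The same four scales, two times | 8 | 33.7% | 26.7% | 21.9% | 16.8% |

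Only the patient scales are counted, because Data analysis makes partners secondary.

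**3. Power if anxiety must succeed at both times.**
SE = 3.75 × √(2/78) = 0.600. Noncentrality = 1.5 / 0.600 = 2.498. Power at one time = Φ(2.498 − 1.645) = 80.3%. Joint power is the bivariate normal probability that both statistics exceed 1.645, assuming a 1.5-point effect at each time and no use of baseline: 67% at r = 0.3, 69% at r = 0.5, 72% at r = 0.7.

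**4. The same rule with baseline adjustment.**
If the model adjusts for baseline anxiety with correlation b to each follow-up, the variance is multiplied by 1 − b² and the follow-up correlation becomes (r − b²)/(1 − b²). With r = 0.5:
- b = 0.3: noncentrality 2.498/√0.91 = 2.619, partial correlation 0.45, joint power 73%.
- b = 0.5: noncentrality 2.498/√0.75 = 2.884, partial correlation 0.33, joint power 81%.

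**5. Keeping several primaries under Bonferroni, at the same standardised effect (1.5/3.75 = 0.4, assumed for every scale).**
Two tests need 99 per arm, four need 119 and eight need 140. With 78 per arm, power is 70.5%, 60.1% and 50.0%.

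**The case against.** The best defence is that this is a condensed article. Multiplicity rules, the deciding contrast and the choice of scale are often left to an analysis plan, which is not shown here. That stands in part. A reader might infer that the trial has no control of its primary error rate, but the document does not support this: it states no rule, which does not show that none exists. Requiring success at both times, or taking one prespecified overall contrast from the mixed model, would hold alpha at 0.05.

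The eight-test family is also a construction. The article writes one-sided 0.05 only for HADS and describes one repeated-measures model for anxiety, not separate tests at each time. Counting all three scales in a joint self-efficacy and empowerment row as primary tests is an assumption. The 34% further requires independence between scales and visits in the same patients, which is implausible, so it is an outer bound and not an estimate. Four empowerment scales would be an overcount, since the fourth belongs to partners.

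Nor can one say flatly that power falls to 69% when both times are required. That figure assumes r = 0.5, equal effects and no baseline adjustment; a well-correlated baseline could restore about 80%. Finally, reading HADS as the anxiety subscale is an easy inference, because Table 1 lists HADS only by subscale and Data analysis makes anxiety primary.

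None of this removes the conflict between the four statements of the primary outcome.

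**Conclusion.** The point holds as an internal contradiction: two places make anxiety and empowerment primary, and two make anxiety alone primary. It does not depend on the unseen analysis plan. The sample size fits only the single-comparison reading, and empowerment has neither a hypothesis nor a power basis.

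The consequence depends on which reading is followed. With two unadjusted tests the error rate is moderately inflated, to about 8 to 10%. The eight-test range of about 17 to 34% marks the outer limit. A both-times rule protects the error rate and puts the cost on power. These figures rest on assumed correlations and, for power, on equal effects at both times. The contradiction itself rests on no assumption and must be fixed.

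**What to change.** Bring the abstract, Study design, Participants and The survey tool into line with Data analysis:

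- Name HADS-Anxiety in patients as the sole primary outcome in every place.
- Name one deciding time point, or one prespecified overall contrast from the mixed model, at the full alpha. Use a single definition of the 3-month visit.
- Make the other time point, carers and empowerment secondary, with one named scale as the main empowerment measure.
- State in Participants that the 1.5-point difference is on HADS-Anxiety at that time point or contrast.

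Keeping two primaries is also legitimate, but it needs a stated alpha rule and a matching sample size: 99 per arm for two Bonferroni-adjusted tests at the same standardised effect.

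The recommended route changes wording only. For one comparison at a named time point, 78 per arm still applies; if an overall contrast is chosen, the SD of 3.75 should be confirmed as applying to it. The registry record was not available and should be checked for the same conflict. The small cost is that empowerment and the second time point lose primary status.

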### Data analysis

Intention-to-treat and per protocol analysis will be conducted. The primary outcome, anxiety will be measured repeatedly across the three time periods and, therefore, analysed using generalised linear mixed models (GLMM). In this context, the GLMMs are similar to linear regression models, but take account of the correlation between repeated measurements on individuals. Their advantage over a traditional repeated measures analysis of variance is that they use all available data under the assumption that missing data are missing at random. Sensitivity analysis will explore the robustness of this assumption. GLMM will also be used to explore the secondary outcome measures. The study is powered on a sample of individual patients. Partners were outside the calculation and are a secondary outcome only.

Qualitative data collected at phone interview (or face to face if possible) at time point 2 will be transcribed, coded and themed to produce a descriptive account of participants’ views about the resource and experiences of using the DVD resource.

### Ethical considerations

The study was approved by Local Health District Research Ethics and University Committees, and registered with the NSW Clinical Trials register. The study will be conducted in accordance with the NHMRC ethical guidelines. Potential participants will be receive an information letter outlining what will be expected of them, informing them of their right to withdraw at any time and guaranteeing their privacy and anonymity and that participation will not impact deleteriously on the care they will receive.

The study was developed in accordance with the Medical Research Council framework for developing and evaluating complex interventions and CONSORT guidelines.

## Discussion

Although blinding is not possible as participants will be aware if they received the intervention DVD or not, it is anticipated that contamination will be minimized because participants will be mainly using the study intervention at home. A particular difficulty for the study is the low numbers of patients who undergo surgery and hence it may take time to get the required numbers.

Meeting the information needs of patients who undergo surgery for head and neck cancers and their families is challenging due to the diversity of tumour site, nature and degree of surgical intervention and unique personal characteristics mean that needs differ from person to person. Further, needs vary over time as confidence levels change and new challenges are encountered.

Improvements in models of care which including the introduction of MDT meetings [27] have increased the opportunities for communication and information provision. However, appointment times are often short and information may not always presented in a way that helps patients and families consider what the experience will mean for them [5]. It is anticipated that using the DVD to inform conversations will help to reduce some of these barriers, helping patients to anticipate and be prepared for the challenges they will face and to gather and strengthen their support networks. Partners and family members’ needs may differ from those of the patient and meeting their needs also contributes to positive outcomes for patients [17]. While some needs have been shown to be similar to those of cancer patients, they may differ in detail and perspective [10] Partners and family members report being more concerned with non-medical topics such as coping with cancer and impact on relationships. The systematic review conducted by [10] highlighted the lack of studies reviewing the information needs of partners and family members in relation to cancers other than breast and prostate. Although not specific to head and neck cancer this review highlights the importance of monitoring needs of both groups and ensuring information is provided that supports the patient and their supporting network.

Little empirical evidence exists that compares means of providing information for patients and partners. The findings of this study will provide evidence that will improve the provision and use of information for patients and their families. It will highlight the role of timely salient information provision in improving patient and carer outcomes after surgery by demonstrating if and how the intervention leads to their increased capacity to cope with and manage their care. In particular it will indicate the impact of the intervention on psychological well-being. It will also demonstrate the effectiveness of an approach to evaluating the use of resources by patients and families. It is anticipated that following evaluation the DVD and accompanying resources will be made widely available for patient benefit nationally and internationally.

## Abbreviations

CNC: Clinical Nurse Consultant
GLMM: Generalised linear mixed models
MINT: Meeting information needs together
RCT: Randomised controlled trial
